			**(months)**
	Demographics	Age, gender, duration of LBP, employment status, educational attainment, medico-legal status	0
Primary	Back pain disability	Roland and Morris Disability Questionnaire	0,3,6
Secondary	Pain	Visual analogue scale	0,3,6
	Distress	Distress and Risk Assessment Method	0,3,6
	Beliefs	Back Beliefs Questionnaire	0,3,6
	Preference based health utility	EQ-5D	0,3,6
	Global perceived benefit	Compared to symptoms at baseline (7 point likert scale)	0,3,6
	Satisfaction scale	Satisfaction with care received (7 point likert scale)	0,3,6
	Objective spinal mobility	Range of motion T-12 & S1	0,3
	Objective physical function	Simmond’s Tests:	0,3
		sit-stand, forward reach, 50-foot walk test	

#### Follow up assessment

Patients will be re-assessed at the clinic at week 12 for follow up of primary and secondary outcome measures. At 6 months, patients will be followed up by postal questionnaire. Maximising completion of follow-up questionnaires will be achieved by (1) texting the patient in advance to inform them that the questionnaire is being sent, (2) enclosing a pre-paid self addressed return envelope, (3) following up with the patient by phone once they have received the questionnaire.

#### Outcome measures

The outcome measures assess the domains of disability, pain, psychosocial and health status, global perceived benefit, satisfaction and functional status (Table 2). The primary outcome measure will evaluate change in functional disability due to LBP measured by the Roland Morris Disability Questionnaire (RMDQ). The RMDQ is widely used in LBP studies in Primary Care and has demonstrated good validity, reliability and responsiveness [31]. All outcome measures demonstrate proven validity and reliability in their particular domain - pain (VAS 0–10) [32], anxiety and depression (DRAM) [33], back beliefs (BBQ) [34], global perceived benefit scale and satisfaction scale (seven point likert scale) [37]. Functional outcomes include sit to stand test, functional reach test and 50 ft. walk test [35] and lumbar spine flexion range of motion [36].

With respect to cost analysis, each patient will be asked to complete a cost diary documenting their medication costs and health care costs (direct costs) for a retrospective three months, prior to attending the clinic and for the prospective six months while participating in the study. The health economic evaluation will consist of a cost benefit analysis and a cost utility analysis, with utility measured by the EuroQol (EQ-5D) [38]. The cost of each treatment strategy will be determined prospectively and includes staff time, overheads and equipment.

### Analyses

All data will be entered into the IBM Statistical Package for the Social Sciences [39] and subsequently cleaned and checked for normality. Baseline differences between the treatment groups will be explored with independent t tests and chi square tests. Preliminary analysis will compare pre to post intervention outcomes for each treatment group to determine if a significant treatment effect is achieved by each of the stratified interventions using paired t-tests and Cohen’s d effect size statistics. The main analysis will compare treatment response between the stratified and control groups using analysis of covariance (ANCOVA) models with baseline measures as the covariate and treatment group as the between group factor. Statistical significance will be set at p < 0.05. Missing data will be imputed using the linear and logistic regression models applied by the multiple imputation functions in SPSS and an intention to treat analysis will be performed. We will also conduct a complete case analysis for those cases where we have complete follow up data. In the event of non normal data, non parametric tests will be performed instead. Exploratory economic analyses will be undertaken. Costs of each intervention will be calculated and quality-adjusted life years (QALYs) gained computed. These will be compared between interventions using independent t tests. Six month health care utilisation attendances and associated costs will be calculated for each patient and compared between the intervention groups using chi square tests for categorical data and t tests for continuous data.

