### Treatment interventions

Following assessment patients will be streamed into one of three treatment interventions based on the STarT Back tool. All interventions will be grouped based and delivered by physiotherapists employed in the Back Screening Clinic.

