#### Low risk intervention

Patients will attend a single 1.5 hour small group session delivered by the physiotherapist promoting active management of their back symptoms and outlining positive messages on maintaining a healthy spine in line with the ‘The Back Book’ [30]. This session will be conducted within a biopsychosocial framework and it’s aim will be to normalise the episode of LBP in line with the guidelines [2]. The benefits of exercise will be emphasised, advice to increase activity levels will be given and information on local exercise centres will be provided. Patients will be instructed with an exercise regime and given a manual which contains information on LBP management, the back exercises and a home exercise log. Each group will consist of three to five patients. The class will also offer the opportunity for patients to ask questions regarding their LBP and self-management. Patients will be encouraged to become more active in their lifestyles and to perform the back exercises on a regular basis.

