#### Medium risk intervention

Patients in this group present with predominantly physical prognostic indicators (disabling LBP, referred leg pain and co-morbid pain) without high levels of psychosocial distress. Patients will attend four 90-minute group exercise/education sessions over four weeks. The content of the educational sessions will include positive messages on managing LBP based on ‘The Back Book’ [30], discussion on the benefits of exercise, a review of spinal anatomy, direction on lifting and handling, ergonomic advice, weight management and the impact of stress, anxiety and low mood on LBP. These sessions will be conducted with a biopsychosocial framework. Patients will be instructed with a stability exercise programme. Each class is a progression from the previous one. All patients will receive a ‘programme’ manual containing general educational information, instruction in each exercise and a home exercise log. Patients will be encouraged to perform the exercises independently at home at least four times/week and to complete the exercise log. Patients will also be encouraged to become more active in their lifestyle and activities such as walking, cycling, swimming or other forms of cardiovascular exercises are encouraged and logged in the activity diaries. Each group will consist of six to ten patients. Patients will maintain the exercise regime independently at home for a further eight weeks following the classes and will subsequently be reviewed at the clinic at 12 weeks. Adherence to the progamme will be monitored by reviewing the patients exercise log weekly and class attendance.

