#### High risk intervention

Patients in this group display high levels of psychosocial distress around their LBP including elements of anxiety, low mood or fear. Physiotherapists administering this component of the intervention will receive extra training in cognitive behavioural therapy (CBT). Patients will attend four 120 min group sessions. The content of this intervention is modelled on the ‘high risk’ intervention delivered in the original STarT Back Trial [10]. Sessions will utilise cognitive behavioural strategies to address unhelpful beliefs and behaviours around LBP. The CBT intervention will include discussion of the bio-psychosocial model of pain, the impact of persistent pain, goal setting based around patient’s functional and social limitations, graded activity, relaxation training, relapse management. It will give the patient’s a better understanding of how they can help themselves and will focus particularly on behaviour change. It will teach the patients to identify and change maladaptive behaviours and use cognitive techniques to identify and challenge unhelpful and unrealistic thoughts and beliefs. This will promote positive behaviour and beliefs about physical activity and avoidance behaviour. Specific psychological and practical skills to promote self management of pain will be developed. Each session will also include an exercise component similar to the medium risk intervention and each patient will receive a ‘programme’ manual containing the relevant information and exercises. Patients will be encouraged to perform the exercises independently at home at least four times per week as well as adopting CBT principles e.g. pacing and goal setting. Each group will consist of four to six patients. Patients will continue the exercise regime independently at home for 8 weeks following the classes and will be reviewed at the clinic at 12 weeks. Adherence to the programme will be monitored by reviewing the patients exercise log weekly and class attendance.

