#### Best care historical control

The historical control consists of patients who attended the clinic between 2009–2011 [25]. Patients were stratified using the STarT Back screening tool but a non-targeted (‘one treatment fits all’) model of care was delivered to patients. All patients undertook the same generic 12 week group education/exercise programme promoting self management and rehabilitation. The efficacy of this intervention has been established [25] and subsequently this template was utilised to develop the medium and high risk interventions. Similar to the medium and high risk interventions, the historical control comprised two phases. In phase one, patients attended once weekly for four weeks and each class was 1.5 hours in duration. Sessions included exercise and back educational information similar to the ‘medium risk’ intervention already described. In phase two, patients continued independently with the structured home exercise programme for a further eight weeks. Each group consisted of six to ten patients. Validated self report and objective physical outcome measures monitored progress at baseline and at 12 weeks. Outcomes utilised included disability (Roland Morris Disability questionnaire (RMDQ)) [31], pain (Visual Analogue Scale (VAS)) [32], distress (Distress and Risk Assessment Method (DRAM)) [33], back beliefs (Back Beliefs Questionnaire (BBQ)) [34], Simmond’s Functional Tests [35] and lumbar flexibility [36].

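### Treatment is delivered in classes of 3 to 10 patients, but the stated tests and the sample size assume independent patients; if outcomes correlate within a class, intervals are too narrow and power is overstated

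*Protocol article*

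**What the plan says.** Delivery is in groups throughout. Under Treatment interventions the article states: "All interventions will be grouped based and delivered by physiotherapists employed in the Back Screening Clinic". Class sizes are then fixed by stratum:

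- Low risk, one session: "Each group will consist of three to five patients".
- Medium risk, four sessions: "Each group will consist of six to ten patients".
- High risk, four sessions: "Each group will consist of four to six patients".
- Historical control, four sessions: "Each group consisted of six to ten patients". These classes were not separated by risk: "All patients undertook the same generic 12 week group education/exercise programme promoting self management and rehabilitation".

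The Analyses section fixes the main model: "The main analysis will compare treatment response between the stratified and control groups using analysis of covariance (ANCOVA) models". The only terms it names for that model are the baseline value and the treatment arm. The other named tests are paired and independent t tests and chi-square tests. No class or therapist term, cluster-robust variance or ICC is mentioned.

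Sample size and statistical power gives 72 per high-risk group and 57 per medium- and low-risk group. The only adjustment it states is the one for ANCOVA.

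**The concern.** Patients in one class share the physiotherapist, the sessions and each other's company. The Background counts meeting people in a similar position among the benefits of group care, and the high-risk sessions include discussion. Some within-class correlation in outcome is therefore plausible, and the plan sets it to zero without saying so.

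If the correlation is positive, the ANCOVA standard error is too small. That would favour both of the trial's hypotheses. Superiority in the high-risk stratum would be declared too readily. So would non-inferiority in the medium- and low-risk strata, because it is judged by whether a 95% confidence limit stays within 1.8 RMDQ points. The stated 80% power would also be too high.

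This is not a detail left to a separate analysis plan, because the article itself names the model and derives the sample size.

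**Working it through.** **Inputs from the article.** Effect size 0.38; two-sided 5%; 80% power; pre-post correlation 0.592; 72 per high-risk group; 57 per medium- and low-risk group, tested at one-sided 2.5%; class sizes as above.

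**Assumptions, not in the article.** ICC of the baseline-adjusted outcome 0.01 to 0.10. Mean new class 5 (high), 8 (medium), 4 (low), the midpoints of the stated ranges. About 2.5 same-stratum patients per control class, since control classes of 6 to 10 mixed three strata in unstated proportions.

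**1. Reproduce the plan's figure.**

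- Unadjusted n per group = 2 × (1.960 + 0.842)² / 0.38² = 108.7, so 109 (110 with the t distribution).
- ANCOVA factor = 1 − 0.592² = 0.6495.
- 109 × 0.6495 = 70.8, so 71; 110 × 0.6495 = 71.4, so 72.

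The stated 72 is thus the independent-patient figure, with a design effect of 1. The 57 leaves no room for a design effect either: it is reached only at one-sided 5% (t-based 87 × 0.6495 = 56.5, so 57), whereas the stated one-sided 2.5% needs 71. That mismatch is a separate matter.

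**2. Variance inflation.** Per arm, DE = 1 + (m − 1) × ICC. With equal arms the variance of the difference is inflated by the mean of the two DEs, and the standard error by r, the square root of that mean. Example, high risk at ICC 0.05: new 1 + 4 × 0.05 = 1.20; control 1 + 1.5 × 0.05 = 1.075; mean 1.1375; r = 1.067.

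**3. Error rate and power (normal approximation).**

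- Actual two-sided error = 2 × [1 − Φ(1.960 / r)]; the one-sided rate is half of that.
- High-risk power = Φ(2.829 / r − 1.960), where 2.829 = 0.38 / (√0.6495 × √(2/72)).

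| ICC | High: mean DE | High: two-sided error | High: power | Medium: mean DE | Medium: one-sided error | Low: mean DE | Low: one-sided error |
|---|---|---|---|---|---|---|---|
| 0 | 1.000 | 5.0% | 81% | 1.000 | 2.5% | 1.000 | 2.5% |
| 0.01 | 1.028 | 5.3% | 80% | 1.043 | 2.7% | 1.023 | 2.6% |
| 0.02 | 1.055 | 5.6% | 79% | 1.085 | 3.0% | 1.045 | 2.8% |
| 0.05 | 1.138 | 6.6% | 76% | 1.213 | 3.8% | 1.113 | 3.2% |
| 0.10 | 1.275 | 8.3% | 71% | 1.425 | 5.0% | 1.225 | 3.8% |

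**4. Sensitivity to the control cluster size.** If all 8 patients of a control class count as the cluster, ICC 0.05 gives a high-risk mean DE of (1.20 + 1.35) / 2 = 1.275, so an error rate of 8.3% and power of 71%. The one-sided error is then 4.6% in medium risk (mean DE 1.35) and 4.0% in low risk (mean DE 1.25).

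**5. Number of classes.** New arm: 72 / 5 ≈ 14 high-risk classes, 57 / 8 ≈ 7 medium-risk classes. With so few medium-risk classes, the normal approximation is if anything optimistic.

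**The case against.** The best counter-argument is that the class effect may be weak. In medium risk, high risk and control, four sessions are followed by eight weeks of independent home exercise. Content follows a manual in one clinic, and the Background itself describes group treatment as more standardised. The primary endpoint is at 6 months, collected by individual postal questionnaire well after the classes end. Low-risk patients meet once, for 1.5 hours. None of this makes the ICC zero, but it argues against the upper part of the assumed range, most of all in low risk.

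A reader might infer more than the documents support in four ways:

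- That the intervals are certainly too narrow in every stratum. This needs a positive ICC, and the article gives none.
- That the medium-risk error rate reaches about 10%. That is the two-sided figure; the planned test is one-sided at 2.5%, so the relevant rate is about 5.0% at most under the main assumptions.
- That all treatment takes place in classes. Only the supervised part does.
- That class membership can be recovered for everyone. The article does not say that class lists for the historical controls were kept.

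The figure of 2.5 same-stratum patients per control class is also an assumption, and step 4 of the working shows that the result depends on it. What survives the objection is that the plan sets clustering to zero without stating or defending it.

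**Conclusion.** The point holds in conditional form. The tests and sample sizes assume independent patients, although supervised care in both arms was given in classes. If outcomes within a class are positively correlated, confidence intervals are too narrow and the 80% power is overstated.

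Under the stated assumptions the size is modest at the lower end of the ICC range and material at the upper end. At ICC 0.05 the high-risk error rate is 6.6% and power 76%; at ICC 0.01 about one power point is lost. The effect is larger if control classes act as whole clusters. It is probably smallest in low risk, where a single session makes the upper ICC values least plausible. The analysis should be amended, but nothing here invalidates the design.

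**What to change.** Record a class identifier for every new-arm patient, and for historical controls where clinic records allow. Fit the same ANCOVA as a mixed model with a random intercept for class and Kenward-Roger or Satterthwaite degrees of freedom. Arm-specific class variances should not be relied on with only about 7 new medium-risk classes.

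If control class membership cannot be recovered, use a partially nested model that clusters the new arm only, and add a sensitivity analysis over a stated ICC range for controls.

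Restate the power of the planned sample over that ICC range. This is disclosure only: recruitment was due to close in June 2013, so enrolment does not change. With results planned for April 2014, the analysis wording can still be amended.

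The cost is a search of clinic records and a change of model wording. The downside is slightly wider intervals and a lower stated power.

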## Methods/Design

### Aims

The main objective of this study is to determine if the implementation of ‘stratified care’ when delivered in a group setting will lead to significantly better physical and psychological outcomes in a group of patients with non specific LBP, compared to a matched best care historical control. The historical control group will consist of individuals who attended the Back Pain Clinic between 2008 and 2011. Evaluation of treatment effect will be made within each of the stratified treatment groups and comparisons will be made between the stratified group outcomes and best care historical control. Secondary analysis will compare the delivery costs of the historical and stratified interventions.

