### Study design

This study is a non randomised controlled trial comparing a new stratified intervention to a historical control treatment, which is usual non-stratified care. The trial is thus pragmatic in nature and aims to establish the effectiveness of a treatment intervention in routine everyday practice [24]. The study will determine if the implementation of stratified care in a group setting, using the STarT Back risk stratification tool will result in significantly better physical and psychological outcomes in LBP patients, compared with historical control data collected between 2009–2011 [25]. Patient assessments will occur at baseline, at 12 weeks and 6 months following commencement of the treatment intervention. The primary endpoint for analysis is 6 months. Recruitment will take place between February 2012 and June 2013.

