This type of study design may be at risk of selection bias, but the choice of historical controls was made to allow comparability of interventions within a single clinical centre, thus removing the risk of differences in management between centres. Furthermore, since the new treatment paradigm necessitated a shift in management approach to include cognitive behavioural principles with subsequent staff training, the selection of historical controls averted any possible loss of fidelity of the routine care treatment which might have occurred if controls were recruited concurrently to the new intervention group. Other measures taken to minimise potential differences between the intervention and control treatments include; the control and historical interventions will be delivered to the same local population, referred from the same sources, using standard diagnostic and referral criteria. Both the historical and new interventions will be applied in the same clinical setting by therapists who will apply the pre and post treatment assessments in a standardised manner. The same end points will be chosen for the stratified treatment group as has been the practice for the historical controls and there will be no time lag between the historical data collection and the stratified intervention phase. This can be considered an appropriate design in the current study setting, where we have a large dataset documenting existing routine evaluation of clinical treatment outcomes [25]. Here the comparison of interest is between the existing standard management of LBP (the historical control group), in a single centre, to a new paradigm of care (intervention).

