**Figure 1 F1:**
[figure not shown]
Study flow chart.

The historical control consists of patients who attended the Back Pain Clinic between 2009–2011. These patients were referred from the 10 GP practices and their associated physiotherapy services within the Waterford City Primary Care area in exactly the same manner as the intervention group. The patients completed a copy of the same self report questionnaires as the intervention group. In the control group, risk stratification was performed by an independent party (administrator at the clinic) after the initial assessment using the STarT Back scoring algorithm. The therapists were blinded as to the risk stratification of each patient until completion of the treatment intervention at three months. Patients in the historical control group were assessed as routine care which included history taking, a physical examination, review of completed self report questionnaires and performance of timed functional outcome measures in exactly the same manner as the intervention group. Following initial assessment if patients were deemed suitable, all patients irrespective of their risk stratification were entered into a generic 12 week group exercise/education intervention. Consent was obtained retrospectively for the inclusion of these historical controls in line with the National Consent Policy [27].

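### The stated main ANCOVA most naturally adjusts only for the baseline outcome score, so measured prognostic differences from the historical controls stay partly unadjusted

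*Protocol article*

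**What the plan says.** Study design in the protocol article sets out the comparison: "This study is a non randomised controlled trial comparing a new stratified intervention to a historical control treatment". The same section concedes that "This type of study design may be at risk of selection bias". Its answer is a set of design measures: one centre, the same local population and referral sources, standardised assessments and the same end points.

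The Analyses section gives the main model as "analysis of covariance (ANCOVA) models with baseline measures as the covariate and treatment group as the between group factor". Before that, "Baseline differences between the treatment groups will be explored with independent t tests and chi square tests". The section does not say what follows from that exploration, and it names no other covariate, no propensity score and no matching.

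The Aims say that the stratified patients are "compared to a matched best care historical control". Neither the recruitment section nor the description of the best care historical control names a matching variable or procedure.

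Table 2 lists these demographic items at month 0: "Age, gender, duration of LBP, employment status, educational attainment, medico-legal status". Pain (VAS), distress (DRAM) and back beliefs (BBQ) are also measured at month 0. For the controls, the recruitment section says that they filled in the same self-report questionnaires, and the description of the historical control lists RMDQ, VAS, DRAM and BBQ among the measures used at baseline and 12 weeks.

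The control period is given in two ways. The Aims refer to "individuals who attended the Back Pain Clinic between 2008 and 2011". The recruitment section says "The historical control consists of patients who attended the Back Pain Clinic between 2009–2011", and Study design and the description of the historical control also give 2009 to 2011.

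**The concern.** Without randomisation, nothing makes the two groups alike on prognosis except what the design and the model control. The design measures standardise where and how patients were treated and assessed. They do not balance who was referred, who was judged suitable or who consented in different years. Consent was also obtained differently: prospectively, after an explanation, for the new patients, and retrospectively for the controls.

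If the groups differ on a factor that predicts RMDQ beyond its own baseline, the ANCOVA estimate contains that difference as well as the treatment effect. The bias could go either way. In favour of the new programme, it inflates the superiority claim for high-risk patients and makes the non-inferiority claim for medium- and low-risk patients easier to reach. Against it, a real benefit could be hidden. Testing baseline differences does not protect against this unless the result is tied to the model.

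The word 'matched' adds to the problem, because a reader would take it that prognostic factors had been balanced by selection. The two control windows leave the comparator group unclear.

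**Working it through.** **1. Which model is planned?** The sample size section gives an effect size of 0.38, 80% power, two-sided alpha 0.05 and a pre/post RMDQ correlation of 0.592, with a reduction for ANCOVA.

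- Per group without covariates: 109 (normal approximation) or 110 (t distribution).
- ANCOVA factor: 1 − 0.592² = 0.6495.
- 109 × 0.6495 = 70.8, rounded up to 71; 110 × 0.6495 = 71.4, rounded up to 72.

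The stated 72 per group is reproduced with the pre/post RMDQ correlation alone. Together with the singular 'covariate' in the Analyses section, this supports reading the model as having one covariate, the baseline score.

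**2. How precise is the adjusted difference?** The plan's SD is 4.7 (SD of change), used with its own ANCOVA factor.

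- Residual SD = 4.7 × √0.6495 = 3.79.
- SE at 72 per group = 3.79 × √(2/72) = 0.63 points.

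**3. What could one omitted covariate do?** The document gives neither the strength of the other prognostic factors nor their imbalance, so both are assumed. Let g be the covariate's effect given baseline RMDQ, in units of the 4.7-point SD per SD of covariate. Let d be the imbalance between groups in SD, also given baseline RMDQ.

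- Bias = g × 4.7 × d.
- Two-sided type I error = 1 − Φ(1.96 − bias/SE) + Φ(−1.96 − bias/SE).

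| g | d | Bias (points) | Share of 1.8 | Type I error, 72 per group |
|---|---|---|---|---|
| 0.1 | 0.1 | 0.05 | 3% | 5.1% |
| 0.1 | 0.5 | 0.24 | 13% | 6.6% |
| 0.2 | 0.25 | 0.24 | 13% | 6.6% |
| 0.2 | 0.5 | 0.47 | 26% | 11.6% |
| 0.3 | 0.25 | 0.35 | 20% | 8.6% |
| 0.3 | 0.5 | 0.70 | 39% | 20.1% |

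**4. Does the choice of residual SD matter?** If 4.7 is the SD of change and the pre and post SDs are equal, the SD of a single RMDQ score is 4.7/√(2 × (1 − 0.592)) = 5.20. The residual SD is then 5.20 × √0.6495 = 4.19, and the SE at 72 per group is 4.19 × √(2/72) = 0.70. The bias in points is unchanged, and the largest type I error falls from 20.1% to about 17%. The conclusion is the same.

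**5. Non-inferiority comparisons.** At 57 per group, SE = 3.79 × √(2/57) = 0.71. A bias of 0.05 to 0.70 points in favour of the new arm raises the one-sided 2.5% error at the 1.8-point margin, 1 − Φ(1.96 − bias/SE), to about 3% to 17%.

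**6. Which covariates are known to exist in both groups?** By the document's own description, RMDQ, VAS, DRAM and BBQ do. Table 2 does not say that its demographic items cover the controls, and the description of the historical control does not list them.

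**The case against.** The strongest reply is that much of the case mix is already handled. The high-risk hypothesis compares like with like on STarT Back risk, and the sample size is set by risk group. The tool covers referred and co-morbid pain, disability, bothersomeness, catastrophising, fear, anxiety and depression. Baseline RMDQ is in the model. This stands. A reader might infer that any change in case mix between the periods would be credited to stratified care; the document does not support that. Only what is left after risk group and baseline score is at issue. Three broad risk levels do leave something.

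Second, 'baseline measures' is plural, and an analysis plan that is not shown could add covariates or say how baseline differences are used. This is possible. But the singular 'covariate' and the reproduced sample size favour the one-covariate reading, and if several were meant the sentence needs rewording. No separate plan would resolve the word 'matched' or the two control windows in this text.

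Third, a reader might assume that every item in Table 2 is available for both groups. That is shown only for the questionnaires. Controls had routine history taking, but the document does not say that employment, education, medico-legal status or pain duration was recorded for them.

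Fourth, a reader might infer from the conflicting dates that the control set could be altered once outcomes are known. Nothing in the document suggests this. It is an inconsistency to correct, with 2008 appearing once and 2009 three times.

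Finally, the article discloses the risk of selection bias and, in its Discussion, the limit on causal inference. Disclosure is to its credit, but it does not replace adjustment for factors already measured.

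**Conclusion.** The point holds in a limited form. As stated, the main model most naturally adjusts only for the baseline value of the outcome in a comparison open to selection bias, and leaves out prognostic measures that the document shows were taken in both groups. Some measured confounding is therefore left in when it could be reduced.

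The amount is unknown. Under the assumed effects of 0.1 to 0.3 SD and imbalances of 0.1 to 0.5 SD, the bias runs from about 0.05 to 0.7 RMDQ points, or 3% to 39% of the 1.8-point difference. The two-sided type I error for the high-risk comparison runs from about 5% to 20%. The low end is negligible, and the document does not show which end is nearer the truth, so the upper figures should not be read as an estimate. They concern one omitted covariate with imbalance remaining after baseline RMDQ.

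Two textual faults do not depend on any assumption: 'matched' has no described matching behind it, and the control window is stated in two ways. The change is worth making because it costs little, not because a large bias has been shown.

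**What to change.** - Within each risk group, prespecify ANCOVA for RMDQ with treatment group, baseline RMDQ and baseline VAS, DRAM and BBQ.
- Add age, sex, duration of LBP, employment, education and medico-legal status where these are confirmed as recorded for the controls. Fix the list before outcomes are compared.
- Optionally, add a propensity-score sensitivity analysis on the same covariates.
- In the Aims, delete 'matched' or describe the matching variables and procedure.
- State one control window throughout, reconciling the Aims with Study design, the recruitment section and the description of the historical control.

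The cost is some wording, a few lines of code and a few degrees of freedom. For VAS, DRAM and BBQ no new data are needed. Demographic items may need retrieval from control records or imputation. Power need not suffer: if the added covariates explain a further 5% to 15% of residual variance (assumed), power at 72 per group is 82.7% to 86.6%, against 80.8% without them, ignoring the variance cost of imbalanced covariates. Adjustment reduces measured confounding only. Unmeasured and calendar-time differences remain, and the report should say so.
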